## EAST-AFNET circulating biomolecules sub-study

- **Specific hypotheses.** Based on our biomedical knowledge, we developed specific hypotheses that will be tested in the EAST – AFNET 4 biomarker sub-study. These include the following:
  1. BMP10 concentrations are associated with recurrent AF and affect recurrent AF differentially depending on the use of sodium channel blockers (flecainide, propafenone).
  2. FGF23 concentrations are associated with recurrent AF.
  3. A combination of ANG2, FGF23, and BMP10 predicts recurrent AF better than natriuretic peptides.
  4. ESM1 concentrations are associated with stroke (both prior stroke at baseline and future stroke during FU) and with the composite of stroke and cardiovascular death
  5. The ABC bleeding score is associated with major bleeding
  6. The ABC stroke score is associated with stroke and with the composite of stroke and cardiovascular death
  7. BNP is associated with heart failure hospitalizations and with the composite of death or heart failure hospitalization
  8. Angiotensin 2, FGF23 (alone or in combination or in combination with ESM1) are strong predictors for stroke or stroke and ACS, or stroke + ACS + CV death

- The 14 circulating biomolecules:
  - ANG2
  - BMP10
  - Cancer-Antigen 125 (CA-125)
  - Cardiac C-Reactive Protein High Sensitive
  - Creatinine (enzymatic determination)
  - D-Dimer [Explicit units would be "ug FEU/mL]
  - ESM1
  - FBP3
  - FGF23
  - Growth Differentiation Factor-15
  - Interleukin-6
  - IGFBP7
  - NT-proBNP
  - Troponin T high sensitive (cTnT-hs)

all numeric, continuous scaled

To enable evaluation of these circulating biomolecules in context with clinical information, a list of parameters that are associated with the primary outcome will be included in the analysis. A preliminary list will be taken from the existing analyses in the trial. If there are too many candidates, we will do some variable reduction to discard “redundant” variables without using the association with the endpoints to inform that decision (e. g. correlations, PCA, etc.).

See supplement to the main results publication for a list of preselected parameters.

- additional **clinical** parameters collected at baseline:
  - age
    - numeric, discrete scaled
  - gender
    - categorical, nominal scaled – dichotomous
  - random group
    - categorical, nominal scaled – dichotomous
- BMI
  - numeric, continuous scaled
- Heart Failure, determined using heart failure symptoms and LVEF
  - categorical, nominal scaled – dichotomous

- EHRA Score at baseline  
Categorical, ordinal scaled
- Center Type (D-Site or A-Site)  
categorical, nominal scaled – dichotomous
- Diabetes mellitus  
categorical, nominal scaled – dichotomous
- History of CAD (MI, CABG or PCI)  
categorical, nominal scaled – dichotomous
- Prior stroke or TIA  
categorical, nominal scaled – dichotomous
- AF pattern  
categorical, nominal scaled
- MoCA Score at baseline  
numeric, discrete scaled
- EQ5D  
numeric, discrete scaled
- 'Systolic blood pressure [mmHg]'  
numeric, discrete scaled
- 'Diastolic blood pressure [mmHg]'  
numeric, discrete scaled
- 'Diastolic LA diameter (maximal diameter) [mm]'  
numeric, discrete scaled
- 'Systolic LA diameter (minimum diameter), optional [mm]'  
numeric, discrete scaled
- Chronic kidney disease (MDRD stage)  
categorical, ordinal scaled
- Heart failure (NYHA classification)  
categorical, ordinal scaled

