- **Secondary outcomes of interest** – Relevant secondary outcomes were estimated at the two-year follow-up visit. These include cognitive function, estimated by the MoCA score; left ventricular function, estimated as ejection fraction in percent; quality of life estimated by the EQ-5D visual analog scale (0-100) and by the SF-12 questionnaire; and rhythm (categorical: sinus rhythm, atrial fibrillation, other). Models will be built to predict these outcomes. Recurrent AF will be defined in two ways: In all patients, AF at the two-year ECG will be used to define recurrent AF. In patients receiving early rhythm control therapy, an unscheduled visit due to AF will be used to define recurrent AF. At a later stage, the analyses of the telemetric ECGs planned in Maastricht will be used to define recurrent AF in patients randomized to early rhythm control. The latter two definitions create an imbalance between the two randomized groups. For continuous parameters, models will be applied to three values, namely 1. The baseline value, 2. The value at two years, and 3. The change between baseline and two years.

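### For hypotheses 1-3 the SAP does not ensure adjustment for rhythm at baseline, so part of an association between a biomolecule and AF on the two-year ECG may reflect rhythm at blood sampling

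*SAP*

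**What the plan says.** **Hypotheses.** In the SAP's list of specific hypotheses, number 1 states that "BMP10 concentrations are associated with recurrent AF and affect recurrent AF differentially depending on the use of sodium channel blockers". Number 2 states that "FGF23 concentrations are associated with recurrent AF". Number 3 states that "A combination of ANG2, FGF23, and BMP10 predicts recurrent AF better than natriuretic peptides". None of the three names covariates.

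**Outcome.** Under Aim of the study, secondary outcomes: "In all patients, AF at the two-year ECG will be used to define recurrent AF". Two further definitions, unscheduled visits for AF and later telemetric ECGs, apply only to patients in the early rhythm control group.

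**Covariates.** After the list of 14 biomolecules, the SAP says that "a list of parameters that are associated with the primary outcome will be included in the analysis". The first co-primary outcome consists of cardiovascular death, stroke or TIA, and hospitalisation for worsening heart failure or acute coronary syndrome. Candidates judged redundant may be dropped, for example on their correlations. The SAP then adds: "See supplement to the main results publication for a list of preselected parameters". The itemised baseline parameters include AF pattern, LA diameter, EHRA score, heart failure and randomised group. Rhythm at baseline or at blood draw is not among them.

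**Rhythm elsewhere.** Rhythm (sinus rhythm, AF or other) appears only as an outcome at two years. The rule that also models baseline values is confined to continuous variables: "For continuous parameters, models will be applied to three values". The subgroups under Further analysis do not include rhythm.

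**The concern.** At enrolment some patients may be in AF and others in sinus rhythm. If a biomolecule is higher while the patient is in AF, and patients in AF at baseline are more often in AF two years later, rhythm at sampling is related to both the marker and the outcome. A model without it can then show an association for a marker that carries no information beyond the rhythm on that day.

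The covariate rule does not guard against this. It selects for association with a cardiovascular composite, whereas hypotheses 1-3 concern later AF. Baseline rhythm is in effect the baseline value of the two-year outcome, and a rule aimed at another endpoint gives no assurance that it will be included.

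At stake is the interpretation of hypotheses 1 and 2 as associations, and of hypothesis 3 as a comparison between markers. That comparison could turn partly on which set of markers tracks rhythm at sampling more closely.

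**Working it through.** **No figure to reproduce.** The SAP gives no power, event rate or effect size for hypotheses 1-3. The check is a reading of the covariate text, followed by a simulation of how large the effect could be.

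**Reading.** The itemised list, the outcome definitions, the sections on models, preprocessing, missing data and balancing, and Further analysis contain no adjustment, stratification or sensitivity analysis by rhythm at sampling. The nearest listed variable is AF pattern, which describes the clinical type of AF and not the rhythm when blood was drawn.

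**Inputs.**
- From the SAP: 1,585 patients (Handling errors and missing data).
- Assumed: 27% with persistent AF; in AF at sampling 75% of these and 37% of the rest, so 0.27 × 0.75 + 0.73 × 0.37 = 0.473, about 47% overall.
- Assumed: the marker is standard normal plus a shift of 0.3, 0.6 or 1.0 SD if in AF at sampling, with no other link to later AF.
- Assumed: two-year AF depends only on baseline rhythm. The contrasts correspond to these odds ratios:
  - 25% vs 20%: (0.25/0.75)/(0.20/0.80) = 1.33
  - 30% vs 20%: (0.30/0.70)/(0.20/0.80) = 1.71
  - 35% vs 15%: (0.35/0.65)/(0.15/0.85) = 3.05
  - 45% vs 10%: (0.45/0.55)/(0.10/0.90) = 7.36

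**Models.** Logistic regression of two-year AF on the standardised marker, two-sided 5%, 300 runs per setting:
- A: logit P(AF at two years) = a + b·marker + c·AF pattern
- B: as A, plus d·baseline rhythm

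**Results, model A (shifts 0.3 / 0.6 / 1.0 SD).**

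| Two-year AF, by baseline AF vs sinus rhythm | Odds ratio per SD | Runs with p<0.05 |
|---|---|---|
| 25% vs 20% | at most 1.06 | 8% / 10% / 12% |
| 30% vs 20% | 1.04 / 1.07 / 1.11 | 10% / 22% / 45% |
| 35% vs 15% | 1.07 / 1.15 / 1.25 | 20% / 70% / 96% |
| 45% vs 10% | 1.14 / 1.27 / 1.46 | 60% / 99% / 100% |

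**Results, model B.** The odds ratio is 0.99-1.01 and the rejection rate 4-7%, about nominal.

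Monte Carlo error matters at this number of runs: near 50% the standard error is √(0.5 × 0.5/300) = 2.9 percentage points, and another set of 300 runs gave 53% where the table has 60%.

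**Other assumptions about AF pattern.** With 30% persistent, AF at sampling in 85% of these and in 20% or 40% of the rest, and two-year AF of 30% or 40% vs 20%, the rejection rate was 9-98% unadjusted, 6-92% with AF pattern and 4-7% with rhythm added. AF pattern removes only part of the effect.

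**Hypothesis 3.** Three rhythm-only markers were compared with one on a 20% hold-out set (shift 0.6 SD, 35% vs 15%, no AF pattern in the models). The trio had the higher AUC in 70% of runs (mean 0.567 vs 0.547). With rhythm in both models it did so in 51% (0.640 vs 0.640). Three noisy readings of rhythm track it better than one.

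**The case against.** **The omission may be only apparent.** The itemised parameters are described as additional, and the main list sits in a supplement that is not shown. Baseline rhythm could be on it. This stands: absence cannot be proved. But that list is presented in connection with the primary outcome, so the SAP does not ensure inclusion, and a variable correlated with AF pattern could be lost in the reduction step.

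**The quoted rule may not govern hypotheses 1-3.** Aim of the study links such parameters to an extended analysis of the primary outcome. This is fair, but no other covariate rule is stated for the recurrent-AF models.

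**The mechanism is assumed.** The SAP does not say that any marker rises during AF. For FGF23, the sole marker in hypothesis 2, no specific reason is offered. This stands, and makes the point conditional.

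**The bias may be small.** With a weak link between baseline and two-year rhythm, which is plausible when half the patients are randomised to early rhythm control, rejection is close to nominal. This stands. The simulation also omits other listed covariates, such as LA diameter and heart failure.

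**A marker that tracks rhythm does predict.** If baseline rhythm predicts later AF, so does the marker, and hypothesis 3 is worded as prediction. If rhythm lies on the pathway from atrial disease to later AF, compulsory adjustment may remove real signal. Both stand. They argue for reporting both analyses, not for leaving rhythm out.

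**Scope and timing.** Only the two-year ECG definition was examined. The SAP does not state when blood was drawn; baseline is implied by the prediction aim. Rhythm on the baseline ECG need not be the rhythm at venepuncture.

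**Conclusion.** The point holds in conditional form. For hypotheses 1-3 under the two-year ECG definition, the SAP does not ensure that baseline rhythm is accounted for, and AF pattern is only a partial substitute. Whether this distorts the results depends on two quantities that the SAP does not give: how far each marker differs by rhythm at sampling, and how strongly baseline rhythm is related to two-year rhythm. Over the assumed ranges the false-positive rate for a rhythm-only marker runs from near nominal to near certain.

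A reader might infer that hypotheses 1-3 will be falsely confirmed, or that any marker sensitive to rhythm has no predictive value. The documents support neither. The first needs figures that are not in the SAP, and the unseen supplement may already supply the covariate. The second confuses prediction with added value beyond the ECG. Nor does the check extend to the definitions based on unscheduled visits or telemetric ECGs.

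**What to change.** Add to the SAP:
- Rhythm on the baseline ECG (sinus rhythm, AF or other), where recorded, is a fixed covariate in all models of two-year rhythm and recurrent AF, whatever its association with the primary outcome, and is exempt from the variable-reduction step.
- For hypothesis 3 it enters both models being compared.
- Results for hypotheses 1-3 are reported with and without it. The unadjusted result answers the pure prediction question; the adjusted result shows what the marker adds to the ECG.
- The time of blood sampling relative to that ECG is stated. If baseline rhythm was not recorded, this is given as a limitation.

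The cost is a short SAP addition, one covariate and a second set of estimates. Trial conduct is unaffected. Associations may shrink, and if rhythm lies partly on the pathway the adjusted estimate is conservative.

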## ***Types of Analysis***

### **Descriptive Analytics**

For all numeric variables the following univariate statistics will be provided:

- mean
- standard deviation
- median
- 25th and 75th quartiles

For all categorical variables the following statistics will be provided:

- absolute frequencies
- relative frequencies

### **Inference Analytics**

It is expected that clinical parameters and biomolecule concentrations will interact in complex ways. These multiple interactions are not well captured by classical regression analyses. On the other hand, multiple regression remains the 'gold standard' in the field. To reflect these complexities and demands, we will train four types of models separately for the 1st primary outcome, the 2nd primary outcome, and the primary safety outcome. Those model types include statistical learning (SL), machine learning, and deep learning (DL) approaches. Furthermore, each of the  $3 * 4 = 12$  models will be trained with clinical confounders and with clinical confounders combined with circulating biomolecules. This gives us the ability to eventually compare 24 models and their reflection of interactions between the clinical parameters and biomolecule concentrations.

- A time-to-event machine learning problem to be solved by different candidate models to be compared against each other. These are namely:
- For 1st primary outcome, 1st primary safety outcome and their components
  - Cox regression – SL - classic approach
  - random survival forest – ML – Tree-based ensemble (bagging)
  - gradient boosted model – ML – Tree-based ensemble (boosting)
  - artificial neural network – DL – multi layer perceptron
- A regression ML-problem to be solved by the following candidate models:
- For 2nd co-primary outcome
  - multiple linear regression – SL - classic approach
  - random forest – ML – Tree-based ensemble (bagging)
  - gradient boosted model – ML – Tree-based ensemble (boosting)
  - artificial neural network – DL – multi layer perceptron

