## ***Model selection***

### **Between model selection**

The best performing model for each of the three ML-problems will be used for further analysis of risk factors. To identify the best model for the regression ML-problem we are going to use **Akaike Information Criteria - AIC** as it is applicable to linear models and non-linear models as well and takes into account model performance and its complexity.

For identifying the best performing time-to-event ML-model we will use the **c-index** and the **Brier Score**.

The information criteria scores will be obtained from applying the model to a hold-out/test dataset of the complete dataset.

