### All variables

A 20 % **hold-out dataset** will be used for evaluating the final model that only relies on the most relevant variables and has been trained on the remaining 80 % of the dataset. At model training time the training set will be further split into **k-fold-cross validation** datasets. The split will be **stratified** for the dependent variable.

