## Handling errors and missing data

For one proband there is a special entry for Variable 'ANG2'. The entry value is 'BLQ' – that stands for Below Limit of Quantitation. Normally those entries will be dealt with as proposed by Bergstrand et al [2]. As we are facing only one entry of this type we are going to set this value to the smallest 'ANG2' value available in the whole dataset.

The remaining dataset has a sample-size of 1585 and missing entries as follows:

- |                          |     |
|--------------------------|-----|
| • Diastolic LA diameter  | 119 |
| • EHRA score at baseline | 97  |
| • MOCA Score             | 42  |
| • LVEF                   | 5   |
| • BMI                    | 4   |

The missing entries will be imputed by SciKit-learn's Iterative Imputer. [3] [4].

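### The SAP pairs models with and without the 14 biomolecules but fixes no criterion for added value, and the only scoring it describes is point values on one 20% hold-out of about 317 patients

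*SAP*

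**What the plan says.** Under Inference Analytics, four model types are planned for each of three outcomes: the first co-primary outcome, nights in hospital, and the primary safety outcome. That makes 3 × 4 = 12, and these "models will be trained with clinical confounders and with clinical confounders combined with circulating biomolecules", giving 24 models to compare.

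Scoring is set out under Between model selection. "For identifying the best performing time-to-event ML-model we will use the" c-index and the Brier score. "To identify the best model for the regression ML-problem we are going to use" AIC. The source of the scores is stated: "The information criteria scores will be obtained from applying the model to a hold-out/test dataset of the complete dataset".

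Under All variables the hold-out is 20% of the data. It serves for "evaluating the final model that only relies on the most relevant variables", and that model "has been trained on the remaining 80 % of the dataset". The split is "stratified for the dependent variable". No repeated split is mentioned, and no other hold-out is described.

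The SAP gives no interval, test, minimum difference or multiplicity rule for the paired contrast. It does not say how c-index and Brier score combine if they disagree.

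**The concern.** The with/without pairs are the SAP's only concrete design for asking whether biomolecules add to clinical information. With only point scores to go on, the analyst must decide what counts as a gain after seeing them. The obvious reading is that the better-scoring model of a pair wins. In about 317 patients the sampling error of a paired difference can be as large as the gain sought, so that reading has no controlled error rate. Useless biomolecules could appear to improve prediction, and modest real gains could be missed.

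**Working it through.** **Nothing to reproduce.** The SAP states no event number, power or error rate for this comparison. Its only arithmetic (12 models, doubled to 24) is correct.

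**Inputs from the SAP**
- Patients: "The remaining dataset has a sample-size of 1585" (Analysis Population gives 1586; the difference is immaterial here).
- Hold-out: 0.20 × 1585 = 317. Training: 1585 − 317 = 1268.
- Added predictors: 14. Clinical predictors: 19 by count of the list.

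**Assumptions**
- Event share 10%, 15% or 20%, so about 32, 48 or 63 hold-out events.
- Clinical c-index about 0.66; clinical R2 for nights 0.10; independent normal predictors.

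**Time-to-event outcomes.** A Cox model with 19 predictors and one with 19 + 14 were fitted to the 80% and scored on the 20%, with 800 runs per cell. The Monte Carlo standard error is at most √(0.25/800) = 1.8 points. The comparator is a 14-df likelihood-ratio test (LRT) on all 1,585 patients. Cells show the % of runs favouring biomolecules at 10/15/20% events.

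| True c-index gain | Hold-out c-index higher | c-index and Brier both better | LRT, all patients |
|---|---|---|---|
| 0 | 33/26/25 | 12/13/13 | 6/5/5 |
| about 0.01 | 43/49/52 | 20/29/36 | 32/48/63 |
| about 0.02 | 58/69/72 | 32/49/55 | 68/87/95 |
| about 0.03 | 76/82/86 | 48/63/72 | 92/99/100 |
| about 0.045 | 86/91/94 | 59/77/86 | 99/100/100 |

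The first row can be checked by hand. Under no gain the paired difference has mean −0.0118/−0.0109/−0.0091, because 14 useless coefficients cost accuracy, and SD 0.0243/0.0169/0.0127. A normal approximation gives P(difference > 0) = Φ(mean/SD) = Φ(−0.49)/Φ(−0.64)/Φ(−0.72) = 31/26/24%, close to the simulated 33/26/25%. A separate run at 10% events gave 29%, against 6% for the LRT.

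Separation is the hit rate minus the false-gain rate, in points:
- Gain 0.01: hold-out c-index 43−33, 49−26, 52−25 = 10/23/27; LRT 32−6, 48−5, 63−5 = 26/43/58.
- Gain 0.02: hold-out c-index 58−33, 69−26, 72−25 = 25/43/47; LRT 68−6, 87−5, 95−5 = 62/82/90.

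**Nights in hospital.** Hold-out AIC = n·log(MSE) + 2p. Fourteen extra terms add 28, so the larger model wins only if log(MSE ratio) > 28/317 = 0.088, a fall in hold-out MSE of 1 − exp(−0.088) = 8.5%. With clinical R2 0.10, an added R2 of 0.03 removes only 0.03/0.90 = 3.3% of residual variance, and 0.05 removes 5.6%. Results over 1,500 linear-model runs:

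| Added R2 | Hold-out AIC favours biomolecules | Hold-out MSE favours biomolecules |
|---|---|---|
| 0 | 0% | 18% |
| 0.01 | 0% | 49% |
| 0.02 | 0.1% | 70% |
| 0.03 | 0.3% | 84% |
| 0.05 | 6% | 93% |
| 0.08 | 45% | 98% |

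For comparison, a joint 14-df F test at 5% on all 1,585 patients has noncentrality 1585 × R2added/(0.90 − R2added). For an added R2 of 0.01 this is 1585 × 0.01/0.89 = 17.8, power about 78%. For 0.03 it is 1585 × 0.03/0.87 = 54.7, power above 99%. This assumes normal errors.

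**The case against.** The SAP nowhere says that the higher score decides whether biomolecules add. Between model selection scores models in order to choose one for further risk-factor analysis. The stated aim is association with severity of heart disease, and relevant biomolecules are to be identified by permutation importance. An extended multivariate analysis is also mentioned under Aim of the study. All of this is true, so the defect is a missing criterion and not a stated bad one. It does not fill the gap: permutation importance works within one model and does not test the pair, and the extended analysis has no details.

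Three stronger readings are tempting and are not supported.

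- *A gain somewhere is the usual result under no effect.* In a binary-outcome simulation at 15% events, at least one of the four model types showed a c-index gain in 73% of null runs. But no section lets any single model establish a gain. In the same simulation the top-scoring model of the eight was clinical-only about 74% of the time. Carrying a c-index rate across all three outcomes is also wrong, because nights are scored by AIC. The two time-to-event composites share death and stroke components, so they are not independent either.
- *The comparison cannot tell a real gain from none.* This is close to true only near a c-index gain of 0.01.
- *The plan is tilted towards biomolecules throughout.* For nights, the linear pair errs in the opposite direction.

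Requiring both c-index and Brier score to improve would cut false gains to 12-13% in the Cox pair, at a cost in sensitivity. The SAP does not state that requirement.

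**Conclusion.** The point holds in limited form: followed as written, the plan yields an added-value contrast without error control. On hold-out c-index alone, the Cox pair's false-gain rate is five to seven times a 5% level (25/5 = 5; 33/5 = 6.6), and true gains of 0.01-0.02 are often missed; larger gains usually show. Hold-out AIC for nights would hide most real gains in the linear pair. For the same Cox data, the full-data test keeps a 5-6% false-positive rate and separates small gains much better.

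The size depends on assumed event shares, clinical c-index or R2, and effect sizes, none of which the SAP gives. Rates for forests, boosting and networks under survival data were not established. The conclusion that no criterion is fixed rests on the text alone.

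**What to change.** For each of the three outcomes, prespecify as the primary criterion of added value one joint likelihood-ratio test, at a stated level. It tests the 14 log-transformed biomolecules added to the clinical Cox model, or to the clinical linear regression of log(nights + 1). Fit it to all actual patients, without the synthetic records planned under Handling unbalanced datasets.

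For each model type, report as supportive the paired difference in performance from repeated cross-validation over the whole dataset, with a 95% interval. Use c-index and Brier score for the time-to-event outcomes and out-of-sample squared error for nights. Resample so that copies of one patient never fall in both training and test folds. State that added value will not be inferred from the single hold-out ranking.

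The cost is SAP wording and some computing time; no new data are needed. Some apparent gains can no longer be claimed. Power for a c-index gain of 0.01 stays moderate (32-63%). The main-effects joint test does not cover the interactions that motivate the machine-learning models; for these, the cross-validated differences remain supportive evidence only.

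### Comparing the performance of 24 models does not isolate interaction between clinical parameters and biomolecules; it can suggest one where none exists and can miss a real one

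*SAP*

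**What the plan says.** The SAP, Inference Analytics, opens with an expectation: "It is expected that clinical parameters and biomolecule concentrations will interact in complex ways". It continues: "These multiple interactions are not well captured by classical regression analyses". This is the reason given for adding machine learning and deep learning to regression: "we will train four types of models separately" for the two co-primary outcomes and the primary safety outcome. Each of the resulting 12 "models will be trained with clinical confounders and with clinical confounders combined with circulating biomolecules". The payoff is then stated: "This gives us the ability to eventually compare 24 models and their reflection of interactions between the clinical parameters and biomolecule concentrations".

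The measures for comparing models are in Between model selection. For the regression problem it is AIC, chosen because it "takes into account model performance and its complexity". For the time-to-event problem: "For identifying the best performing time-to-event ML-model we will use the c-index and the Brier Score". These are computed on held-out data. The only hold-out share in the SAP is 20% (Data preprocessing, All variables).

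Three other places bear on interaction. The first of the Specific hypotheses says that the effect of BMP10 on recurrent AF depends on sodium channel blocker use. Further analysis foresees separate models by sex, age group and other classes. Permutation feature importance is the tool for identifying relevant biomolecules. None of the three comes with a product term or a test of interaction.

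**The concern.** A statement about interaction needs a contrast that is null when there is no interaction. Neither contrast available among the 24 models has that property.

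- Clinical set versus clinical set plus biomolecules, same algorithm: null when the biomolecules add nothing. Main effects are enough to break it.
- Forest, boosting or network versus Cox or linear regression, same predictors: null when both classes predict equally well. A threshold or U-shape in a single variable breaks it. So does tuning, which Inside model selection applies only to the flexible learners. In the other direction, the extra variance of a flexible learner can hide a real interaction.

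No model is compared with its own interaction-free version. At stake is what gets reported: a curved effect of one biomolecule could be described as a biomolecule-by-clinical interaction, or a real interaction could be overlooked because regression predicted as well.

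**Working it through.** **The plan's own figure.** 3 outcomes × 4 model types = 12; × 2 predictor sets = 24. This reproduces. Per outcome there are 4 × 2 = 8 models, distinguished by algorithm and predictor set only.

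**Hold-out size.** 0.20 × 1,586 = 317 patients (Analysis Population gives 1,586; using the 1,585 in Handling errors and missing data also gives 317).

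**Simulation, continuous outcome.** From the SAP: N = 1,586, 317 held out, 14 biomolecules. Assumed: 18 clinical variables, standard normal predictors, biomolecules correlated at 0.25 with each other and independent of the clinical variables, residual SD 1, and the effect sizes. Linear regression, gradient boosting (depth 3, early stopping) and random forest were fitted with each predictor set and compared on hold-out mean squared error, 80 runs per row (Monte Carlo standard error at 65%: √(0.65 × 0.35 / 80) ≈ 5 points). Gain means the fall in error when biomolecules are added. The last two columns are a 1-df F test of the one true product term in all patients, at 0.05 and at 0.05/252 (18 × 14 = 252 pairs).

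| Truth | Boosting or forest beats linear | Boosting gain > linear gain | Forest gain > linear gain | Test, 0.05 | Test, 0.05/252 |
|---|---|---|---|---|---|
| Linear, no interaction | 19% | 34% | 31% | 4% | 0% |
| Curve and step, no interaction | 65% | 86% | 70% | 2% | 0% |
| Interaction 0.12 SD | 26% | 39% | 42% | 100% | 89% |
| Interaction 0.20 SD | 39% | 51% | 61% | 100% | 100% |

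With a true interaction, no tree-based learner won in 100 − 26 = 74% and 100 − 39 = 61% of runs. Even the difference in gains, the contrast closest to interaction, exceeded zero most often in the row with curvature and no interaction.

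**Predictor-set contrast.** In a separate run of 100 replicates with linear effects and no interaction, adding biomolecules lowered the hold-out error in 99% for both linear regression and boosting.

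**Other outcome types.** Both assume 20% events, 20 clinical variables and 14 biomolecules, N = 1,585.

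- Censored survival times, boosted Cox (depth 3) beating Cox on hold-out c-index, 100 runs per scenario: additive linear 20%; steps without interaction 65%; U-shape without interaction 91%; one interaction with coefficient 0.25, 26%, and 0.40, 36%. A likelihood-ratio test of the product term rejected in 3–5% without interaction and 99–100% with it.
- Binary outcome, boosting beating logistic regression on AUC, 200 runs: additive 22%; steps 67%; U-shape 74%; biomolecule × age interaction of 0.25, 32%, and 0.40, 41%; biomolecule × arm interaction of 0.30, 27%. The likelihood-ratio test rejected in 3.5–7% and 90–100%.

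**Sensitivity to the assumed effects.** A further binary simulation (34 independent predictors, 20% events, 100 runs) gave: additive 15%; quadratic coefficients of 0.1, 0.2 and 0.3 without interaction 12%, 22% and 33%; three and six interactions of 0.4, 36% and 50%; three and six of 0.6, 76% and 85%.

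**Not simulated.** AIC, the Brier score, the neural network and the random hyper-parameter search. The first two are also whole-model measures, so the argument about what the contrasts can isolate carries over; the percentages may not.

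**The case against.** The SAP's aim is to find biomolecules associated with outcome and to predict outcomes. It expects interactions and does not announce a test for them, and choosing flexible learners for that reason is ordinary practice. AIC, c-index and Brier score are assigned to choosing a model for the later risk-factor analysis. A reader might infer that the plan will credit interaction whenever boosting wins and declare it absent whenever Cox wins. The SAP states no such rule, so that reading is not supported.

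A reader might also infer from the simulations that the comparison favours the flexible learner more often without interaction than with it. That is not a general result. Against an additive linear baseline of 22%, the binary simulation gave 27–41% with interaction. The order reverses only when strong curvature is placed in the no-interaction scenarios. With several strong interactions, the kind of structure the SAP expects, the flexible learner won in 76–85%.

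The product-term test is flattered too: it was handed the true pair and used all patients. Correction over 252 pairs still left 89–100% power, but only for the continuous outcome and the assumed effects.

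The age-group models in Further analysis are a second route to interaction. They are optional, and no test of difference between the groups is stated.

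These points limit the claim to what the comparison can do. They do not supply a contrast that isolates interaction, and the sentence stands in the section on inference.

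**Conclusion.** The point holds in this limited form. The comparison of 24 models is presented as reflecting biomolecule-by-clinical interactions, and nothing in it separates interaction from main effects, non-linearity, tuning or sampling noise in about 317 patients. It can suggest an interaction that is absent and can miss one that is present. In the continuous-outcome simulation the false signal ranged from 19% to 65% and the missed interaction from 61% to 74%. These figures illustrate the problem and do not forecast this study's results, because the SAP gives no effect sizes or event rates. The subgroup models and the BMP10-by-sodium-channel-blocker hypothesis have no stated interaction test to fill the gap. The defect should be corrected, but it does not undermine the main aim of identifying biomolecules.

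**What to change.** In Inference Analytics, delete the claim that comparing the 24 models reflects interactions, and say that differences between model classes are reported as differences in prediction only.

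Add an interaction analysis within the planned regression models (Cox, linear, and a suitable regression for recurrent AF). Fit flexible main effects, for example splines for continuous variables, with and without a short pre-named list of product terms. Include BMP10 × sodium channel blocker use and biomolecule × age. Use likelihood-ratio tests on all patients with multiplicity control such as Holm. The flexible main effects matter because, with correlated predictors, unmodelled curvature can leak into a product term.

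Boosting with depth-1 trees, which is additive, may be compared with the tuned depth, but as description only. On a single hold-out in the survival simulation, depth 3 beat depth 1 in 19–34% of runs without interaction and 39–52% with it, which is weak separation. Repeated cross-validation may help but was not checked.

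The cost is a wording change and a few more fits on existing data. The downside is that only the pre-named pairs receive a formal test.
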